### Primary and secondary outcomes

Primary and secondary outcomes are summarized in Table 1. The primary outcome measure is the difference in time-to-exhaustion during the endurance treadmill test (run at the HR corresponding to 85% of V̇O_2_ max) between the probiotic and placebo groups after a 6-week intervention. Changes will be adjusted for corresponding baseline time-to-exhaustion values. Longer time to exhaustion is a desired outcome for runners and offers a performance advantage in a competitive environment.

**Table 1 Tab1:** Descriptions of the study outcome measures

Outcome	Description
Primary	
Time-to-exhaustion during treadmill endurance run	During an endurance treadmill run performed at the heart rate (HR) corresponding to 85% maximal rate of oxygen consumption (V̇O_2_max), the participant will run until voluntary time to exhaustion (reflected by meeting 2 out of 3 criteria: respiratory quotient ratio (VCO_2_/VO_2_) ≥ 1.1; HR reaches a minimum of 85% of age-predicted maximal HR (220 minus age); rating of 17 on the 6 to 20 point Borg Rating of Perceived Exertion scale (BRPE).
Secondary	
Blood chemistries	Capillary blood samples will be collected before, during, and after the treadmill endurance test to determine concentrations of glucose and lactate. These metabolites will be quantified using commercial, handheld colorimetric devices (ContourNext EZ glucose meter, LactatePlus lactate meter).
Body composition	This variable will be assessed using the scale (to assess weight) and BOD POD®, a body composition measuring device that measures fat mass and lean muscle mass. Coefficients of variation are 12%, and ICC are 0.9 [20].
Borg Rating of Perceived Exertion Scale (BRPE):	Exertion is a subjective estimate of exercising intensity. This self-reported instrument assesses effort and fatigue due to physical work [21]. Ratings range from 6=no muscle effort to 20=maximal muscle effort possible, cannot work any harder.
Bristol Stool Scale (BSFS):	Is a 7-point, self-rated scale of changes in stool form (hardness, shape, water content) that corresponds to intestinal transit time (*r*=−0.65) [22]. This tool is being used to monitor responses to the intervention and is supported for use in gastrointestinal research.

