The secondary outcomes, which will compare probiotic and placebo groups while adjusting for the corresponding baseline values, are as follows: (A) Borg Rating of Perceived Exertion (BRPE) [21] at peak lactate threshold during the endurance treadmill test (represents greater perceived tolerance to running workload); (B) exercise-induced changes in blood chemistry, specifically glucose concentrations and lactate threshold during the endurance treadmill test (reflects fuel use patterns during running); (C) biomarkers of stress (salivary cortisol and alpha-amylase) and biomarkers of immune activity (salivary secretory immunoglobulin A; sIgA); (D) cold/flu symptoms (severity, duration and number of episodes) as self-reported on the daily questionnaire [23]; (E) gastrointestinal function and discomfort as assessed by the weekly administration of the Gastrointestinal Symptoms Rating Scale (GSRS) [24] and (Digestion-associated Quality of Life Questionnaire (DQLQ) [25] and stool frequency and consistency (Bristol Stool Scale; BSFS) [22] as self-reported on the daily questionnaire; and (F) change in body composition (% fat, % fat-free mass, fat-free mass, fat mass, and body mass) from baseline between the probiotic and placebo groups.

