**Table 2 Tab2:**
[figure not shown]
Schedule of activities per visit

^a^A week before the randomization and the final visits

^b^Questionnaires are administered daily, starting 14 days before the randomization visit until 7 days after the end of the intervention (muscle soreness, cold-flu symptoms, stool frequency-consistency)

^c^Questionnaires are administered weekly starting 2 weeks before the Randomization visit until 1 week after the end of the intervention (GSRS, BSFS, DQLQ)

^d^Questionnaires are administered at baseline and final visits (sHEI, Fiber Screener, BREQ-3)

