### Statistical methods

The primary outcome will be tested using a linear model to determine if the adjusted mean response value differs between groups adjusting for baseline values. For secondary outcomes that measure the statistical difference in response between intervention groups (blood chemistries, perceived exertion, and salivary measures), a linear model will be used to determine if the mean response value differs between groups, adjusting for baseline values. Where relevant, differences between groups will be adjusted for sex as well as the corresponding baseline. For secondary outcomes that are only measured during the intervention period, the response between intervention groups (number of days sick, duration, and severity) will be tested by using a two-sample *t*-test. All analyses mentioned above will be performed with the intent-to-treat and per protocol populations. The per protocol population is defined as compliant participants who took at least 80% of the study supplement during the 6-week intervention period.

All hypotheses will be tested using two-sided tests with a type I error rate of *α* = 0.05 using the SAS v9.4, JMP Pro v14 (SAS Institute Inc., Cary, NC, USA), or SigmaPlot v14 (Systat Software, Inc.) software. For the continuous response data with models that require the normality of residuals and a homogeneous variance, the residuals will be assessed using plots of the standardized residuals in four ways: versus the predicted values, in a histogram, in a Q-Q plot versus the expected value under the assumed distribution, and in a boxplot. Should there be a failure of model assumptions then transformations will be applied, or non-parametric tests will be used where appropriate. The most common transformations used adjust for a skewness and heterogeneity in variance are the natural log, log base 10, or a square root transformation. If data are transformed for analysis, the least square means will be back-transformed for reporting and the standard errors of the back-transformed means will be estimated using the Delta method ^29^.

No imputation will be performed for missing variables where there is only a single outcome measured. Variables assessed daily but analyzed weekly (such as frequency and consistency of stool samples) will be averaged in the case of missing data. The variables assessed daily will be compared as the daily average per week.

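### Stool consistency is compared only as a weekly mean Bristol score, in which hard and loose stools offset each other, so a fall in both kinds can be partly or wholly hidden

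*Protocol article*

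**What the plan says.** Under Primary and secondary outcomes, secondary outcome E (gastrointestinal function and discomfort) includes "stool frequency and consistency (Bristol Stool Scale; BSFS"), self-reported on the daily questionnaire. Table 1 describes the scale thus: "Is a 7-point, self-rated scale of changes in stool form (hardness, shape, water content) that corresponds to intestinal transit time".

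The Statistical methods section places stool consistency under a daily-to-weekly rule: "Variables assessed daily but analyzed weekly (such as frequency and consistency of stool samples) will be averaged in the case of missing data". The next sentence gives the summary to be compared: "The variables assessed daily will be compared as the daily average per week". No other summary of stool form appears in the article, such as days with hard stools, days with loose stools, or distance from mid-scale.

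The footnotes to Table 2 disagree on collection. Footnote b lists the daily items as "muscle soreness, cold-flu symptoms, stool frequency-consistency". Footnote c reads: "Questionnaires are administered weekly starting 2 weeks before the Randomization visit until 1 week after the end of the intervention (GSRS, BSFS, DQLQ").

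**The concern.** The Bristol scale runs from hard to loose. The protocol itself treats both directions as symptoms: in Table 1 the GSRS places hard stools under its constipation subscale and loose stools under its diarrhea subscale. That the middle of the Bristol scale is normal and both ends abnormal is the usual reading, though the article does not state it.

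On that reading, a runner whose stools alternate between hard and loose has the same weekly mean as a runner with mid-scale stools every day. Across runners, hard stools that soften and loose stools that firm up pull the group mean in opposite directions. Eligibility does not select for constipation or for loose stools, so nothing in the design makes the expected change one-directional. Gastrointestinal health is a stated secondary objective, and the only planned summary of stool form can miss a benefit that lies in fewer extreme stools.

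The weekly mean is a stated choice, so this is not a detail left to an unseen analysis plan. The non-parametric fallback in Statistical methods does not help, because the offsetting happens when the average is formed, before any test.

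**Working it through.** The plan gives no figure for this outcome, so there is none to reproduce.

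**Inputs from the article.** Weekly mean of daily scores; 7-point scale; 16 per arm (Sample size); two-sided 0.05 (Statistical methods).

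**Assumed inputs.** Abnormal means types 1–2 (hard) or 6–7 (loose). Abnormal days are 40% on placebo and 20% on probiotic. Hard days score 1 or 2 equally often (mean 1.5) and loose days 6 or 7 (mean 6.5). Other days score 3, 4 or 5 with mean 4. One week of 7 days, no baseline adjustment, and the same abnormal-day rate for every runner within an arm.

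**Step 1: single weeks.**
- 2, 2, 6, 6, 4, 4, 4: sum 28, mean 28/7 = 4.0, four abnormal days.
- 4 on all seven days: mean 4.0, no abnormal day.
- 1, 1, 2, 4, 6, 6, 7: sum 27, mean 27/7 = 3.86, six abnormal days.

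Complete normalisation of the first or third pattern moves the mean by only 0 or 0.14 points.

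**Step 2: expected group difference.** With hard share h and abnormal rate q, the mean is 4 + q × [1.5h + 6.5(1 − h) − 4] = 4 + 2.5q(1 − 2h). Probiotic minus placebo is 2.5 × (0.20 − 0.40) × (1 − 2h) = 0.5(2h − 1).

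**Step 3: power.** Two-sample t-tests, 4,000 simulated trials per setting. The lower figure in each range is for runners who each lean one way, the higher for hard and loose days mixed within a runner.

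| Hard share of abnormal days | Shift in mean | Power, weekly mean | Power, proportion of abnormal days |
|---|---|---|---|
| 50% | 0.00 | about 5% | about 90% |
| 60% | 0.10 | 6–9% | about 89% |
| 75% | 0.25 | 14–24% | 89–90% |
| 100% | 0.50 | about 79% | 89–90% |

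Hand check of the last column: SE = √[(0.4×0.6/7 + 0.2×0.8/7)/16] = 0.060, and 0.20/0.060 is about 3.3, which agrees with 90%.

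**Step 4: hard and loose proportions taken separately.** At a 50:50 split each falls from 20% to 10% of days.
- Mixed within runners: SE = √[(0.2×0.8/7 + 0.1×0.9/7)/16] = 0.047; 0.10/0.047 = 2.1; power about 53% for each.
- Each runner leaning one way: per-runner variances are 0.5×0.24/7 + 0.25×0.4² = 0.057 and 0.5×0.16/7 + 0.25×0.2² = 0.021; SE = √[(0.057 + 0.021)/16] = 0.070; 0.10/0.070 = 1.4; power about 27% for each.

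The 90% therefore belongs to the pooled proportion, not to each separate one. Using all six weeks and adjusting for the pre-baseline proportion would be expected to raise the separate figures.

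**Step 5: the reverse case.** Let average stool form shift from 3.75 to 4.25 on an underlying scale, with between-person SD 0.5 and within-person SD 0.9 (total √(0.25 + 0.81) = 1.03). At 3.75, hard days are Φ((2.5 − 3.75)/1.03) = 11.2% and loose days 1 − Φ((5.5 − 3.75)/1.03) = 4.5%, together 15.7%. At 4.25 the two figures swap and the total is again 15.7%. With 16 per arm and 42 days, the mean has about 75% power and the pooled proportion about 5%. Neither summary is enough alone; separate hard and loose proportions show the swap.

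**The case against.** Four points can be made for the plan, and much of each stands.

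**The scale is tied to transit time.** Table 1 gives a correlation of −0.65 with transit. Transit runs in one direction, so a mean is a proper summary of it. A reader might infer that the weekly mean is invalid, or that a shift toward loose stools would be reported as a benefit. The article supports neither: tests are two-sided and no direction is labelled favourable. The mean answers one question and is silent on another.

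**Other outcomes carry the hypothesis.** The stated hypothesis concerns fewer gastrointestinal symptoms, and the GSRS scores constipation and diarrhea separately. This narrows the gap but does not close it, because the GSRS rates symptom severity and not recorded stool form.

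**Full cancellation is the extreme case.** It needs an even hard/loose split, and the article gives no mix. The 40% and 20% are illustrative, in healthy adults with gastrointestinal disease excluded. The loss is still large at 75:25 and modest only when nearly all abnormal stools lie on one side.

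**The sentence sets a unit of summary, not a testing scheme.** A reader might infer six separate weekly tests, with a false-positive risk to match. The wording fits a single repeated-measures model of weekly averages just as well, and that model is commonly left to an analysis plan. Nor does the sentence govern the GSRS or DQLQ, which are weekly instruments, so it gives no ground for changing their analysis.

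**Conclusion.** The point holds in a limited form. The only planned summary of stool form lets hard and loose stools offset each other, so a reduction in both can be partly hidden or, if they are evenly split, wholly hidden. In the assumed scenario the power of the mean runs from about 5% to about 79% depending on the mix, against about 90% for the proportion of abnormal days. This rests on reading both ends of the scale as abnormal, on the assumed 40% and 20%, and on uniform abnormal-day rates within an arm, which makes the absolute power figures optimistic. The contrast between the two summaries matters more than either level.

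It would go too far to conclude that the mean should be replaced by a pooled abnormal proportion: step 5 shows that this can miss a pure transit shift, which the mean detects.

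The conflict between footnotes b and c is plain on the text and bears on the remedy, since the averaging rule and any count of days both need daily scores.

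This concerns one component of one secondary outcome. The primary outcome is unaffected and the GSRS subscales give partial cover. It is a minor improvement.

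**What to change.** - Keep the mean Bristol score and label it as the summary of average transit.
- Before unblinding, preferably before the sponsor reveals which codes are paired, pre-specify two further summaries over the six-week intervention: the proportion of reported days (or stools) with hard forms and, separately, with loose forms. Name the Bristol types that count as each. Compare each between groups, adjusting for the pre-baseline proportion and sex.
- Reconcile Table 2: stool consistency is daily in footnote b and in the outcome description, while BSFS is weekly in footnote c. If only weekly scores exist, the day-based proportions cannot be formed.

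**Cost.** If collection is daily, this changes analysis wording only; recruitment was still open at the stated protocol version, so it can be settled in time. It adds two secondary comparisons, with a small multiplicity burden, and dichotomizing loses some information. Each separate proportion also has less power than the pooled one (step 4), so the estimates and confidence intervals should be read together with the mean.

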### Frequency of auditing trial activity

Study case report forms will be reviewed on a weekly basis by a minimum of two investigators for quality control. Considering that this trial is low risk and of short duration, no interim analysis is planned. Monthly auditing checks will be conducted by the study sponsor to review adverse events, protocol deviations, supplement management, and recruitment numbers. Additionally, monitoring visits will be conducted by the study sponsor every 6 months.

### Communication of protocol amendments to relevant parties

All proposed protocol changes will be reviewed by study personnel and must be agreed upon between the study site and study sponsor before seeking IRB approval of the amendment.

### Dissemination plans

Study findings will be disseminated at scientific conferences and by publication in the trial registry or in a peer-reviewed journal by the members of the study team.

## Conclusion

The study protocol described here was designed to gather insight into the ergogenic effects of a probiotic in non-elite athletes. Additionally, the current study will assess the effects of the probiotic on gastrointestinal and immune health in non-elite runners. These results will help build the evidence base necessary for documenting the role of probiotics in non-elite athletes, with the ultimate goal of identifying additional options to help runners improve their performance and possibly overcome some of the intestinal or immune discomforts caused by running.

## Trial status

The trial is currently enrolling participants and in the data collection phase. Protocol version 1.2, July 2, 2021, is being used. Recruitment began in February 2021 and is estimated to be completed in February 2022.

## Data Availability

After publications of the results, deidentified data will be shared with qualified researchers and scientists upon reasonable request to the sponsor including a detailed proposal of the intended use of the data as per the Lallemand Health Solutions Inc. Policy on Clinical Trial Transparency and Data Sharing (available upon request).

## Abbreviations

ACSM: American College of Sports Medicine
BREQ-3: Behavioral Regulation in Exercise Questionnaire
BMI: Body mass index
BREQ3: Behavioral Regulation in Exercise Questionnaire
BRPE: Borg Rating of Perceived Exertion
BSFS: Bristol Stool Scale
CFU: Colony-forming units
DQLQ: Digestion-associated Quality of Life Questionnaire
ELISA: Enzyme-linked immunosorbent assay
GSRS: Gastrointestinal Symptoms Rating Scale
HR: Heart rate
RQ: Respiratory quotient
sHEI: Short Healthy Eating Index
sIgA: Secretory immunoglobulin A
VCO2/VO2: Carbon dioxide production/oxygen consumption
V̇O_2_ max: Maximal rate of oxygen consumption
